### Statistical analysis

Data analysis of the primary outcome will be based on the full analysis set constructed by the intention-to-treat principle, whereby patients will remain in their original group regardless of contamination. The per-protocol set will also be analyzed by sensitivity analysis for the primary outcome to evaluate whether contamination impacts the direction of the effect. The secondary outcomes will also be compared based on the per-protocol set. The need to impute missing values will be determined by the proportion of and reasons for missing data. If imputation is necessary, appropriate methods, such as the last observation carried forward, “best-worst-case” scenario and multiple imputation regression modeling, will be chosen according to the distribution of the missing values.

Data analysis will be conducted separately for the randomized and nonrandomized groups, and consistency of effect directions between the two sets of analyses will be evaluated. For the randomized groups, repeated-measures analysis of variance will be employed for the continuous variables measured each month; QoL and symptom scale scores will be compared by *t* tests, and categorical variables will be compared by chi-square tests. These analyses will not be adjusted for covariates unless there are factors that are significantly unbalanced at baseline. For nonrandomized groups, we will utilize repeated-measures ANOVA, linear mixed models, and logistic regression models depending on the data distribution; potential confounders will be adjusted for, including age, body mass index (BMI), baseline SBP, duration of hypertension, type of antihypertensive regimen, diabetes, dyslipidemia, smoking, and alcohol consumption. The between-group difference will be measured by the mean differences for continuous outcomes (i.e., changes in SBP, DBP, dosage of antihypertensive drug, QoL, and hypertensive symptom scores) and the risk ratios (RRs) for binary outcomes (i.e., the response to treatment and incidence of new-onset cardiovascular events).

We are also interested in whether there are different blood pressure lowering effects between HSM regimens with different parameters, which will be explored by the following subgroup analyses with prespecified effect directions based on our clinical experience:

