A high degree of heat-sensitized sensation is expected to be associated with better efficacy than a low degree. A scale developed in-house will be used to measure the degree of heat-sensitized sensation. The scale includes four dimensions (depth/range/distance [not available for three systemic reactions], intensity, frequency, and comfort) for 12 sensations (Additional file 2). Each dimension can receive a score of 0 to 5 points. A patient whose total score in the four dimensions for any sensation is ≥ 60% (i.e., 15 points) will be considered to have achieved a high degree of heat-sensitized sensation. This scale was tested in a sample of 64 patients and showed good reliability and validity—the Cronbach alpha coefficient was 0.892, and the factor loadings for all items were > 0.6.HSM ≥ 4 times per week is expected to be associated with better efficacy than HSM < 4 times per week.Heat-sensitized sensations at both the main and matching acupoints are expected to be associated with better efficacy than heat-sensitized sensations at only the main acupoint.The development of nonthermal sensation (the last 7 moxibustion sensations on the scale) is expected to be associated with better efficacy than the development of only thermal sensation.

In addition, subgroup analyses comparing patients who underwent compulsory and voluntary randomization will be carried out to validate the impact of patient preference on the effects.

If the HSM group shows a better response to treatment than the control group, we will perform an economic evaluation in which the cost-effectiveness ratio and incremental cost-effectiveness ratio will be used as indicators. If a better response to treatment is associated with the frequency of HSM, the balance between the costs of moxibustion materials and outcomes will be explored. A cost-effectiveness acceptability curve will be applied to visualize information about uncertainty in the cost-effectiveness analysis.

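### The graded sensation score is tested against SBP lowering only as high v low at one unsupported cut; if the score is roughly normal with a linear effect, this loses about 36% of the information or more

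*Protocol article*

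**What the plan says.** All of this stands in the protocol article, under Statistical analysis, unless another section is named.

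- **Aim.** The authors ask whether there are "different blood pressure lowering effects between HSM regimens with different parameters, which will be explored by the following subgroup analyses". These analyses are exploratory, with directions fixed in advance from clinical experience.
- **Hypothesis.** "A high degree of heat-sensitized sensation is expected to be associated with better efficacy than a low degree".
- **Scale.** "The scale includes four dimensions (depth/range/distance [not available for three systemic reactions], intensity, frequency, and comfort) for 12 sensations". "Each dimension can receive a score of 0 to 5 points". A sensation with all four dimensions therefore runs from 0 to 20, and a systemic reaction with three dimensions from 0 to 15.
- **Cut.** A patient who reaches 60% of the total (the article also gives this as 15 points) on any one sensation "will be considered to have achieved a high degree of heat-sensitized sensation".
- **Support.** The scale was developed in-house and tested in 64 patients. The article reports internal consistency ("the Cronbach alpha coefficient was 0.892") and factor loadings. Both concern the items, not the cut.
- **Data.** The Visit schedule section says that heat-sensitized sensations are recorded at each follow-up visit as a basis for subgroup analysis. It does not name the scale score.

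**The concern.** The scale yields a graded measure, but the only planned comparison is between two classes. That treats patients just either side of the cut as fully different and patients far apart within a class as the same. The answer then depends on where the cut was put. A patient can be classed as high through any one of 12 sensations, so nothing makes the split even, and an uneven split usually costs more.

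Information is scarce here. The question concerns HSM patients only: 60 + 20 = 80 randomized and 120 nonrandomized, and the plan analyses the two sets separately. After the plan's 20% attrition allowance, 80 becomes 64. At stake is the chance of seeing whether stronger sensation goes with better SBP lowering, an association that the authors expect and that bears on how HSM is thought to work.

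**Working it through.** **Inputs from the article.** Two-sided alpha 0.05, power 80%, difference 5 mmHg, SD 8 mmHg, attrition 20%, and HSM arms of 60, 20 and 120 (Sample size estimation). Dimensions scored 0 to 5 and Cronbach alpha 0.892 (Statistical analysis).

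**Assumptions, because the article gives none.** The distribution of the score, the share classed as high, and the size of any SBP difference by sensation. The SD of 8 mmHg is taken to apply to SBP change within the HSM arm.

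**1. The plan's own figure.** The article gives no power for this subgroup. Its main sample size reproduces: 2 × ((1.960 + 0.842)/5)² × 8² = 40.19 per group, and 40.19/0.8 = 50.2, hence 51. This confirms the reading of SD and alpha used below.

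**2. Information kept by a cut.** For a normal score with a linear effect and a share p classed as high, the efficiency relative to the score is φ(z_p)²/[p(1 − p)]. The third column is 80 × efficiency. The last column is Φ((1.960 + 0.842) × √efficiency − 1.960), the power left where the score analysis would have 80%.

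| Share high | Kept | Lost | 80 patients are worth | Power left |
|---|---|---|---|---|
| 50% | 0.637 | 36% | 51 | 61% |
| 30% | 0.576 | 42% | 46 | 57% |
| 20% | 0.490 | 51% | 39 | 50% |
| 10% | 0.342 | 66% | 27 | 37% |

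**3. In mmHg.** For an even split, the standardized effect with the cut is diff/(8 × √(4/n)). With the score it is that value divided by √0.637 = 0.798. Power is Φ(effect − 1.960).

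For n = 64 and diff = 4: 4/(8 × 0.25) = 2.00, so power is Φ(0.04) = 52%. With the score, 2.00/0.798 = 2.51, so power is Φ(0.55) = 71%.

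| Assumed difference between halves | n = 64, cut v score | n = 80, cut v score |
|---|---|---|
| 3 mmHg | 32% v 47% | 39% v 56% |
| 4 mmHg | 52% v 71% | 61% v 80% |
| 5 mmHg | 71% v 88% | 80% v 94% |

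The gain is about 14 to 19 percentage points over this range.

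**4. If the score is not normal.** Loss was computed as 1 − corr(score, high indicator)², still with a linear effect.

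- Simulated 0-20 totals of four 0-5 items, with inter-item correlation 0.892/(4 − 3 × 0.892) = 0.67: 32-73% lost at a cut of 12 and 30-94% at a cut of 15, depending on where the scores lie.
- Highest of three such sensations: 35-71% over the two cuts.
- Uniform score: 25-27% at cuts of 10 to 12, and 37-39% at a cut of 15.
- Strongly two-clustered score: 17% at a cut of 12 and 27% at a cut of 15.

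Both 12 and 15 were tried because 60% of 20 points is 12, while 15 of 20 is 75%. That discrepancy is a separate matter, and settling it would not remove the loss. It does change how many patients count as high.

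**The case against.** The strongest reply is that the plan tests exactly what it hypothesizes. It states a contrast of high with low, not a gradient, and the Background describes heat-sensitized sensations as something patients do or do not experience. A reader might infer that the trial prespecifies a dose-response; the text does not say so. If the true effect is a threshold and the cut sits near it, the cut loses little and a straight line is the wrong model. This stands, and it is why the fix includes a check of shape.

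A reader might also infer that at least a third of the information is always lost. That is the minimum only for a normal score with a linear effect; step 4 shows smaller losses. Normality is unsupported for the best of several ratings among patients who had to show at least one sensation to enter the HSM group.

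The 4 mmHg difference is an assumption, and large beside the 5 mmHg expected for HSM v control. The power figures also take an even split and a single SBP change, and so ignore the planned monthly measures. They illustrate the size and do not forecast it.

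The analysis is exploratory, "which will be explored by the following subgroup analyses with prespecified effect directions based on our clinical experience", and one prespecified cut does prevent a search for a favourable one. A prespecified slope prevents that equally well. Any rationale for the cut may lie in Additional file 2, which was not available, so the statement is only that the article cites none.

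Finally, a percentage of the maximum across unlike sensations is not shown to be an interval scale. That limits how literally a slope can be read, but the same pooling of sensations underlies the high/low class.

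**Conclusion.** The point holds as a minor improvement to an exploratory analysis. The article fixes a single-cut comparison of a graded score, cites no support for the cut and describes no analysis of the score.

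If the score is roughly normal and linearly related to SBP change, the loss is about 36% at an even split, 42% at 30/70 and 51% at 20/80. At an assumed 4 mmHg and an even split, power is 52% rather than 71% with 64 patients. A uniform score cut near its middle or a two-cluster score would lose about 17-27%, and a well-placed threshold effect also less. Without the score distribution the actual loss cannot be stated.

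Nothing here touches the primary comparison or the sample size, and the documents do not support reading it as a flaw in either.

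**What to change.** In the first subgroup analysis, make the graded score the tested term:

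1. Take each HSM patient's highest sensation score as a percentage of that sensation's attainable maximum, which allows for the three systemic reactions with one dimension fewer.
2. Prespecify one summary over visits, for example the mean of the follow-up visits.
3. Enter it as a continuous covariate in the model for SBP change, adjusted for baseline SBP, separately in the randomized and nonrandomized HSM patients.
4. Report the slope with its 95% CI, for example in mmHg per 10 percentage points, and check the shape with a spline or tertiles.
5. Keep high/low as a descriptive display.

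Confirm that the scale score, not only the presence of sensations, is recorded at the visits used. If it is, no further data are needed.

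The cost is a few lines of analysis text. A slope is slightly less simple to present than two groups and needs the linearity check.

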Overall, HSM has the potential to become an appropriate technique for the management of hypertension in the community because it is simple, convenient, effective, and inexpensive. For example, moxa heat stimulation at acupoints has been demonstrated to induce positive changes in the levels of renin activity, atrial natriuretic peptide, and aldosterone in plasma, resulting in a reduction in blood pressure [13]. HSM is also considered to reduce blood pressure by modulating the expression of the mammalian target of rapamycin and decreasing the level of oxidative stress in the body [14]. A meta-analysis including 18 randomized controlled trials (RCTs) found that moxibustion reduced systolic blood pressure (SBP) by 7.85 mmHg and diastolic blood pressure (DBP) by 4.09 mmHg in patients with primary hypertension over a median 4-month course, although it should be noted that the evidence was not for HSM specifically and the quality of evidence was affected by the risk of bias [15]. The HSM technique is also easy to learn and perform; after receiving a short training session, patients can administer moxibustion at home, by themselves or with the help of family members. Moreover, self-administration of HSM becomes more convenient with the use of a moxibustion device (e.g., moxibustion jar).

Nevertheless, implementing HSM for the treatment of hypertension in the community still requires evidence regarding the following critical questions: Does RCT evidence support that HSM is effective for hypertension? Can HSM replace some doses of antihypertensive drugs? What are the safety, compliance, and cost-effectiveness of HSM for hypertension in the community setting? To answer these questions, we plan to perform a pragmatic RCT with patient preference consideration. We hypothesize that adding daily HSM self-management to traditional antihypertensive treatment/no treatment will result in better blood pressure control efficacy than the original antihypertensive regimen, with good safety and lower costs. Given the real-world situation that patients in community settings may adapt different antihypertensive regimens, this pragmatic trial will be based on an add-on comparison (i.e., HSM + original antihypertensive regimen vs. original antihypertensive regimen) to validate the hypotheses, which will also facilitate maintaining patients’ original preference in the patient-preference arms and observing changes in dosage of antihypertensive drugs over the study period.

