#### Secondary outcomes

A change in mean DBP (mmHg) at month 6 as measured with SBP.The response to treatment at month 6, which is defined as an SBP reduction of ≥ 20 mmHg or DBP reduction of ≥ 10 mmHg for all patients, achieving SBP < 140 mmHg and DBP < 90 mmHg for patients ≥ 65 years or SBP < 130 mmHg and DBP < 80 mmHg for patients < 65 years [17].A change in the mean dosage of the original antihypertensive drug at month 6. At each visit, the physician will decide whether to adjust the original antihypertensive regimen administered to control blood pressure within the ideal range according to the blood pressure measurement, which will be recorded to assess this outcome.A change in mean QoL at month 6, as assessed by the Euro-QoL-5 Dimensions-5 Levels (EQ-5D-5L) questionnaire [19]. This questionnaire includes five items that evaluate QoL in terms of mobility, self-care, usual activities, pain/discomfort, and anxiety/depression. Each item receives a score from 1 to 5 (1, optimal QoL; 5, extremely poor QoL), and a comprehensive index value is calculated from these items, ranging from 0 (extremely poor QoL) to 1 (optimal QoL). The questionnaire also has an overall health status item assessed by a visual analog scale and scored between 0 and 100. A higher score indicates a better overall health status.A change in the mean severity of hypertensive symptoms scored by the symptom scale in the Guiding Principles of Clinical Research on New Drugs of Chinese Medicines at month 6 [20]. The scale assesses 24 hypertension-related symptoms. Each item receives a score of 0 to 3, and a higher score indicates higher severity of that symptom; the total score is the sum of the individual item scores and ranges from 0 to 72 (see details in Additional file 1).Incidence of new-onset cardiovascular events at month 6, including angina, myocardial infarction, and stroke. These data will be collected from patients and family self-reports.Patient compliance with HSM at each visit. This will be determined by the dosage of each administration and the weekly frequency of applications.Cost-effectiveness at month 6, as calculated by comparing the ratio of total treatment cost (China Yuan) to the rate of patients who achieve the targeted response to treatment between the HSM and control groups. Total and antihypertensive treatment costs will be analyzed. Outpatient and inpatient treatment frequencies and costs will also be compared.

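### The incremental economic evaluation is run only if HSM shows an undefined better response, although the protocol lists cost-effectiveness as an unconditional outcome

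*Protocol article*

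**What the plan says.** The protocol article deals with cost-effectiveness in four places.

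- **Statistical analysis:** "If the HSM group shows a better response to treatment than the control group, we will perform an economic evaluation". Within that evaluation, "the cost-effectiveness ratio and incremental cost-effectiveness ratio will be used as indicators". The same paragraph adds: "A cost-effectiveness acceptability curve will be applied to visualize information about uncertainty in the cost-effectiveness analysis". That sentence does not repeat the condition, but by its position the curve belongs to the conditional evaluation.
- **Secondary outcomes:** "Cost-effectiveness at month 6, as calculated by comparing the ratio of total treatment cost (China Yuan) to the rate of patients" who reach the response target, compared between groups. No condition is attached. Two further unconditional statements follow: "Total and antihypertensive treatment costs will be analyzed" and "Outpatient and inpatient treatment frequencies and costs will also be compared".
- **Abstract, Methods:** the cost-effectiveness ratio is listed among the things to be evaluated, again with no condition.
- **Background:** the hypothesis is that adding HSM "will result in better blood pressure control efficacy than the original antihypertensive regimen, with good safety and lower costs". The same section asks whether HSM can replace part of the drug dose.

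**The concern.** Two things go wrong if the conditional sentence governs.

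First, it conflicts with the outcome list. The cost-effectiveness ratio is always calculated according to one section and sometimes calculated according to another. Which applies depends on a trigger that could mean a positive point estimate or a significant difference.

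Second, the trigger depends on the outcome. Similar response at a different cost is a result of interest here, because the trial asks about drug replacement and hypothesises lower costs. In that case the reader would see cost differences and response differences separately, with no statement of the two together. The same holds if HSM costs more and does not improve response. When the trigger is met, the response gain entering the incremental ratio comes only from trials in which the gain was favourable. It is therefore too large on average, and an acceptability curve drawn afterwards does not allow for that.

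**Working it through.** **The protocol's own figures.** It gives no response rate, cost or economic sample size, so there is no stated figure on this point to reproduce. The only usable input is the number randomised (Sample size estimation): 60 per group compulsory + 20 per group voluntary = 80 per arm. With the planned 20% attrition, 80 × 0.8 = 64.

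**Assumptions.** Control response of 40% (range 30–60%); true differences of 0, 0.10 and 0.20; trigger applied to the randomised comparison. 'Better' is read either as an observed difference d > 0 (lenient) or as two-sided p < 0.05 in favour of HSM (strict).

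**Hand calculation, 40% vs 50%, 80 per arm (normal approximation).**

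SE = √(0.40×0.60/80 + 0.50×0.50/80) = √(0.24/80 + 0.25/80) = 0.078

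For a threshold c, let a = (c − 0.10)/SE. Then P(run) = 1 − Φ(a), and E[d | run] = 0.10 + SE × φ(a)/(1 − Φ(a)).

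- Lenient, c = 0: P(run) = 0.899, E[d | run] = 0.115.
- Strict, c = 1.96 × SE: P(run) = 0.248, E[d | run] = 0.200.

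With equal true response the same approximation gives P(run) = 0.50 (lenient) or 0.025 (strict).

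**Check by binomial simulation** (400,000 trials per setting, pooled-variance test, 80 per arm, control 40%; range over control 30–60% in brackets):

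| True difference | Lenient: run | Lenient: mean d if run | Strict: run | Strict: mean d if run |
|---|---|---|---|---|
| 0 | 0.468 (0.468) | 0.066 (0.062–0.067) | 0.024 (0.024–0.026) | 0.182 (0.168–0.186) |
| 0.10 | 0.884 (0.884–0.894) | 0.117 (0.115–0.117) | 0.238 (0.238–0.265) | 0.202 (0.192–0.202) |
| 0.20 | 0.994 (0.994–0.997) | 0.201 (0.201) | 0.715 (0.715–0.802) | 0.237 (0.225–0.237) |

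The lenient run rate under equal response falls from 0.50 to 0.468 because exact ties do not count as better. With 64 per arm the inflation is slightly larger: at a true 0.10 and control 40%, the means are 0.124 (lenient) and 0.222 (strict).

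**Effect on the ICER.** ICER = ΔC/ΔE. Take a positive ΔC that is unrelated to the observed response, and insert the mean selected ΔE. The true-to-reported scaling is then 0.10/0.115 = 0.87 (lenient) or 0.10/0.20 = 0.50 (strict). At a true difference of 0.20 it is 0.20/0.201 ≈ 1.00 or 0.20/0.237 = 0.84.

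**The case against.** Three stronger readings are tempting, and the protocol does not support them.

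- **Equal response at lower cost would never be evaluated.** A reader might infer this from the conditional sentence alone. The Secondary outcomes analyse total and antihypertensive costs and compare outpatient and inpatient use and costs, all unconditionally. Change in drug dosage is also an unconditional outcome. A cost saving would be visible. If that section governs, the average cost-per-responder ratios would be reported too. Only the incremental comparison and its uncertainty would be lost.
- **Any ratio reported is selected to look favourable.** Selection acts on response, not on cost. If HSM costs more, the ICER may still be poor. Under the lenient reading, small positive differences pass and give very large ratios.
- **The ICER is halved.** That needs the strict reading, a true gain of only 10 points and a positive incremental cost. Under the hypothesised lower costs with better response, HSM would dominate and the size of the ICER has no clear meaning.

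It might also be said that the plan relies on average ratios. It does not rely on them alone, since the Statistical analysis section already names an ICER and an acceptability curve. How far drug adjustment at visits would bring response rates together is not known. The Interventions section says the original regimen is maintained, while the Secondary outcomes allow the physician to adjust it.

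These objections limit the size of the problem. They do not remove the contradiction between sections, the undefined trigger, or the upward selection of the effect. An explicit rule that conflicts with the article's own outcome list is not a detail left to an analysis plan.

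**Conclusion.** The point holds in a limited form. The protocol makes the CER, the ICER and, by implication, the acceptability curve depend on an undefined favourable response, while elsewhere it states cost-effectiveness as an unconditional outcome.

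The selection bias runs from negligible to about twofold in the incremental effect. It is small on the lenient reading when there is a real gain of 10 points or more, and largest on the strict reading with a modest true gain. If true response is equal, the evaluation is skipped in roughly half of trials or in nearly all of them, whatever the costs. All of these sizes rest on assumed response rates and on 80 analysed per arm. The contradiction itself rests on no assumption. One secondary outcome is affected, and the primary SBP comparison is untouched.

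**What to change.** Delete the condition in the Statistical analysis section and bring that section into line with the Abstract and the Secondary outcomes. State that incremental cost and incremental response will be reported whatever the response result, with their joint uncertainty shown by the acceptability curve already planned. Give the ICER where it is interpretable. Where the response difference is close to zero, or one group is both cheaper and better, say so in place of a ratio. Make the change before response results by group are seen.

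No new data are needed, because treatment and expenses are already recorded at each monthly visit (Visit schedule). The cost is a wording change and a little more analysis work.
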